## Abstract

**Background:**

Contingency management (CM) is an evidence-based intervention providing tangible rewards as positive reinforcement for abstinence from stimulants such as methamphetamine. Integrative approaches targeting affect regulation could boost the effectiveness of CM in community-based settings and optimize HIV/AIDS prevention efforts.

**Methods/Design:**

This randomized controlled trial with HIV-positive, methamphetamine-using men who have sex with men (MSM) is examining the efficacy of a 5-session, individually delivered positive affect regulation intervention – Affect Regulation Treatment to Enhance Methamphetamine Intervention Success (ARTEMIS). ARTEMIS is designed to sensitize individuals to non-drug-related sources of reward as well as assist with managing depression and other symptoms of stimulant withdrawal during CM. HIV-positive, methamphetamine-using MSM who are enrolled in a community-based, 12-week CM program are randomized to receive ARTEMIS or an attention-matched control condition. Follow-up assessments are conducted at 3, 6, 12, and 15 months after enrollment in CM. Four peripheral venous blood samples are collected over the 15-month follow-up with specimen banking for planned biomarker sub-studies. The primary outcome is mean HIV viral load. Secondary outcomes include: sustained HIV viral suppression, T-helper cell count, psychological adjustment, stimulant use, and potentially amplified transmission risk behavior.

**Discussion:**

Implementation of this randomized controlled trial highlights the importance of delineating boundaries between research activities and community-based service provision. It also provides insights into best practices for integrating the distinct agendas of academic and community partners in clinical research. This trial is currently enrolling and data collection is anticipated to be completed in September of 2018.

**Trial registration:**

This trial was registered on clinicaltrials.gov (NCT01926184) on August 16, 2013.

## Background

There is increasing recognition that individuals who use stimulants such as cocaine, crack, or methamphetamine experience profound HIV-related health disparities [1]. HIV-positive men and women who use stimulants display substantially elevated HIV viral load, which appears to be primarily due to difficulties with anti-retroviral therapy (ART) adherence and persistence [2–4]. Consequently, HIV-positive men and women who engage in more frequent stimulant use are at elevated risk for faster HIV disease progression [5–7]. The co-occurrence of elevated HIV viral load and HIV transmission risk behavior among HIV-positive, stimulant-using men who have sex with men (MSM) also results in amplified risk of onward HIV transmission [8, 9]. As a result, there is increasing interest in testing substance abuse interventions with HIV-positive, stimulant-using MSM with the goal of increasing rates of sustained HIV viral suppression to optimize the effectiveness of HIV treatment as prevention [10, 11].

Contingency management (CM) is an evidence-based, behavioral intervention where individuals receive tangible reinforcement for biologically confirmed substance abstinence that has been tested as a stand-alone intervention and shown to boost the effectiveness of cognitive-behavioral therapy with stimulant users [12, 13]. Although randomized controlled trials (RCTs) provide support for the efficacy of CM for decreasing stimulant use among substance-using MSM [14, 15], the effects are moderate and not consistently sustained over long-term follow-up. Similarly, a previous RCT with HIV-positive opiate and cocaine users observed decreases in HIV viral load as well as HIV risk behaviors immediately following CM, but these were not maintained over follow-up [16]. These short-term benefits may be partially attributable to the difficulties individuals can experience with achieving abstinence during CM [17] and the underscore the need for more intensive treatment with those who have chronic, relapsing substance use disorders [18]. In San Francisco, the Department of Public Health has been successfully implementing a 12-week CM intervention with methamphetamine-using MSM since 2004 as one component of more comprehensive substance abuse treatment services tailored for MSM [19–21].

Novel approaches are needed to assist methamphetamine-using MSM with managing symptoms of stimulant withdrawal that potentially undermine the effectiveness of CM. Negative reinforcement models of addiction [22] highlight that increases in depression and other forms of negative affect during withdrawal are a potent, chronic stressor that can serve as a trigger for stimulant use in MSM [23]. Consequently, interventions that provide coping skills training and promote psychological resilience could boost and extend the effectiveness of CM. Informed by Revised Stress and Coping Theory, positive affect (e.g., happiness, gratitude) may reinvigorate coping efforts in the midst of chronic stress and build supportive social networks that assist individuals with managing stressful circumstances [24, 25]. Lending support to its potential adaptive significance, positive affect is associated with decreased sexual risk taking behavior in MSM and enhanced HIV disease management [26–28]. These findings are generally consistent with the beneficial associations of positive affect with health and well-being in other populations [29], but important questions remain regarding whether this reflects personality factors or if the experience of more frequent positive affect is linked to better outcomes [30].

Positive affect interventions could boost the effectiveness of existing approaches to promote health behavior change, and more clinical research is needed with HIV-positive substance users. One RCT with hypertensive African Americans observed that a positive affect intervention delivered with patient education increased medication adherence at 12 months compared to patient education alone, but no concurrent intervention-related effects on blood pressure were observed [31]. Similarly, another RCT with patients receiving a percutaneous coronary procedure observed that a positive affect intervention delivered with patient education increased physical activity by almost 2-fold at 12 months compared to patient education alone [32]. Among those with alcohol and substance use disorders, positive affect interventions may increase responsivity to non-substance-related sources of reward, sustain cognitive-behavioral change processes that are relevant to recovery, and help build social relationships that are crucial to reducing or avoiding substance use [33, 34]. One pilot RCT of a web-based gratitude intervention with individuals receiving outpatient treatment for an alcohol use disorder observed short-term increases in low activation positive affect compared to an attention-control condition [35]. We also completed a pilot RCT with methamphetamine-using MSM where a positive affect intervention delivered during CM achieved short-term increases in positive affect compared to CM alone [36]. Building upon this formative clinical research, we present the protocol for a Phase II RCT of a positive affect intervention designed to serve as an adjuvant to CM with HIV-positive, methamphetamine-using MSM.

## Method and design

This Phase II RCT is examining the efficacy of a 5-session positive affect intervention that is designed to boost and extend the effectiveness of CM with HIV-positive, methamphetamine-using MSM (www.clinicaltrials.gov; NCT01926184). All enrolled participants are referred to a community-based, 12-week CM program that must be initiated prior to randomization. CM visits are completed at the San Francisco AIDS Foundation and all other trial-related activities occur at a separate field site in the community. Screening and enrollment are anticipated to continue through June of 2017 and follow-up assessments will be completed in September of 2018. All relevant procedures are approved by the Institutional Review Boards for the University of California, San Francisco and Northwestern University, and this RCT received a certificate of confidentiality from the National Institute on Drug Abuse. The data safety and monitoring plan is overseen by the University of California, Los Angeles Data Safety and Monitoring Board for Addiction Medicine, which holds annual meetings to review participant-related events and overall progress for this RCT.

### Recruitment, screening, and enrollment for the RCT

HIV-positive, methamphetamine-using MSM are recruited for this RCT through three primary sources. First, men initiating services at a community-based CM program complete a brief consent form to be contacted by study staff to learn more about the RCT. Second, direct recruitment is conducted using flyers and palm cards that are distributed in HIV medical clinics, AIDS service organizations, bars and clubs, bath houses, and via social media. Third, an incentivized snowball sampling method is employed where eligible participants receive a maximum of $30 for referring up to three individuals who are subsequently judged to be eligible for the RCT.

To be eligible for this RCT, participants must meet the following inclusion criteria: 1) 18 years of age or older; 2) identify as a MSM; 3) provide documentation of HIV-positive serostatus (i.e., letter of diagnosis or ART medications other than Truvada that are matched to their photo identification); and 4) provide a urine or hair sample that is reactive for methamphetamine metabolites. All potentially eligible participants referred from the community-based CM program are scheduled for an in-person screening visit. Participants recruited from other sources are required to report methamphetamine use in the past 30 days to be eligible for an in-person screening visit.

At the in-person screening visit, participants complete a signed informed consent, consent for specimen banking, a detailed tracking form with at least one secondary contact, and a consent to search relevant death registries. Participants also complete a Health Insurance Portability and Accountability Act (HIPAA) release to access treatment records at the CM program. Those who provide a urine sample that is reactive for methamphetamine or have documented evidence of a reactive urine screen for methamphetamine from the CM program are immediately scheduled for a baseline assessment. Those without evidence or recent methamphetamine use from urine screening provide a hair sample for toxicology testing. Hair is collected from the occipital region of the scalp where possible, but it is also collected from other sites (i.e., beard, body) where necessary to obtain biological confirmation of recent methamphetamine use. After the screening visit, participants receive a $50 pre-loaded debit card. Participants are excluded after the screening visit for the following reasons: 1) prescription of a psychostimulant (e.g., Adderall) that cross reacts with urine screening for methamphetamine; 2) inability to provide informed consent; 3) unable to follow the study protocol; and 4) judged by the principal investigators that it is not in the best interests of the individual to participate.

### Community-based CM program

This RCT is being conducted in partnership with a community-based, 12-week CM program for methamphetamine-using MSM that is operated by the San Francisco AIDS Foundation. Individuals who are interested in the CM program complete a detailed intake that includes assessments of the frequency with which they use methamphetamine and engage in sexual behaviors with men. MSM who report using methamphetamine at least weekly on average in the past three months provide a urine sample for toxicology screening at the intake visit and are enrolled in the CM program irrespective of urine toxicology results.

All clients in the CM program are encouraged to pursue abstinence from methamphetamine and other stimulants during the 12-week CM period. Urine sample collection is directly observed by CM program staff. The voucher for the initial sample that is negative for methamphetamine and cocaine metabolites is worth $2.00. Vouchers increase in value by 25 cents for each consecutive stimulant-free sample to a maximum of $10.00. Participants earn an $8.50 bonus voucher for every third consecutive stimulant-free sample. A rapid reset procedure allows participants to return to their place in the escalating reinforcement schedule after producing three consecutive urine samples that are non-reactive for methamphetamine and cocaine [19]. The total possible reinforcement is $330, and participants may choose to receive incentives earned any time during or after the 12-week CM intervention period.

Concurrent with the CM urine screening visits, clients may participate in a drop-in group that provides social support for continuing to pursue goals for stimulant use reduction or abstinence. Drop-in groups also provide opportunities to facilitate linkage to community-based services including formal substance abuse treatment and HIV care. After completing the 12 weeks of urine screening visits, individuals are invited to attend aftercare sessions to continue to forge social networks that are supportive of avoiding stimulant use and develop relapse prevention plans. Those who complete the 12-week CM program with aftercare are invited to continue attending regular drop-in groups to provide support and mentorship to men who are actively completing the thrice weekly urine screening visits.

### Run-in period and randomization

All eligible participants complete a run-in period where they are required to complete five separate visits prior to randomization. These visits include: 1) a baseline assessment with a peripheral venous blood sample; 2) three urine screening visits (regardless of the toxicology results) at the community-based CM program; and 3) a separately scheduled randomization visit where the first intervention or attention-control session is administered. Participants who fail to complete the run-in period are not randomized and do not complete subsequent visits for this RCT unless at some point they re-initiate contact with the study team and choose to be re-screened. Randomization is accomplished using a computer generated sequence with randomly permuted block sizes of 2, 4, and 6 to guard against subversion. Only the study data manager has access to the computer-based randomization algorithm. Because randomization occurs at the first intervention or attention-control session, this ensures that all participants in this RCT complete at least one of the five individually delivered sessions.

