### Outcome analyses

We will first generate one-way frequency tables for all variables and measures of central tendency and variability for continuous variables (e.g., means, medians, standard deviations) to perform range checks, quantify the amount of missing data, and yield valuable descriptive findings. Chi-square tests, *t*-tests, and comparable two-group non-parametric tests will be used to investigate equality of potential confounders (e.g., homelessness) across the intervention and attention-control conditions at baseline. Similarly, we will confirm that there are no differences in the mean number of intervention and attention-control sessions completed as well as no differential attrition by study arm.

Based on our extensive experience working with this population, we anticipate a maximum of 20% attrition over the 15-month investigation period. Attrition analyses will compare respondents who complete all measurements to those who do not based on baseline characteristics and we will test for differential attrition by intervention condition. Direct maximum likelihood and multiple imputation will be used to address incomplete data because these methods make the relatively mild assumption that missing data arise from a conditionally missing-at-random process [60].

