Intent-to-treat analyses will be conducted primarily using multilevel random coefficient models (i.e., hierarchical linear modeling; HLM). These models incorporate random intercepts and slopes for each participant based on the participant’s multiple measurements over time [61]. Initial models will be unadjusted and compare outcome trajectories for participants in ARTEMIS + CM and Attention-Control + CM across time via the group-by-time interaction effect. If preliminary analyses detect imbalance in potential confounders across the groups that cannot be satisfactorily addressed via covariate adjustment, we will substitute causal inference methods based on the Rubin causal model (e.g., propensity score weighting; marginal structural models) to obtain population-level effects of the intervention under the assumption of balanced confounders between the two groups [62–66]. A priori planned comparisons will be performed to test group differences at 3, 6, 12, and 15 months for both the primary and secondary outcomes. These planned comparisons will be evaluated at α = .05; any subsequent post-hoc comparisons will be adjusted via simulation-based stepdown methods to maintain a nominal Type I error rate of .05 [67].

The primary outcome will be log_10_ HIV viral load over the 15-month follow-up. Sustained HIV viral suppression will be examined as a secondary outcome using logistic regression of the binary outcome of sustained virologic suppression over the 15-month follow-up (0 = no; 1 = yes) on randomization group assignment. Other continuous secondary outcomes that will be examined in intent-to-treat analyses include: CD4+ T-cell count, positive and negative affect, stimulant craving, and self-reported stimulant use. Ordered categorical and categorical outcomes assessed repeatedly over the 15-month follow-up include: ART adherence and persistence, a positive urine toxicology result for stimulants, potentially amplified transmission risk partners stratified by methamphetamine use, and any potentially amplified transmission risk.

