### Power analysis

Using NCSS PASS with a total sample size of 150, 80 % retention, and four repeated measures of viral load, the minimum detectable effect sizes are in the small-medium range (Cohen’s *d* = 0.29–0.47). Estimates of the minimum detectable effect size vary depending on the within-subject correlation. Overall, this RCT has adequate power to detect moderate effects of ARTEMIS + CM on the primary outcome, log_10_ HIV viral load.

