Conducting a community-engaged RCT with a CM program has also required a greater focus on clearly delineating roles and responsibilities. Although participants complete a HIPAA release to allow for communications with the CM program, this is for the expressed purpose of establishing eligibility for randomization, to extract the CM urine screening results and CM incentives received from the clinical records, and assist with tracking for follow-up. Due to our close and ongoing interactions with the CM program, the research team must avoid discussions that are relevant to the clinical care participants are receiving in the CM program and strive to disclose only the minimum information necessary to CM program staff regarding each participant’s study activities. Similarly, our close connection with the CM program can create role confusion for participants that contributes to a therapeutic misconception [70]. This requires staff to have detailed and ongoing discussions with participants about the distinctions between participating in this RCT and receiving clinical services. Staff note their ethical obligation to ensure the safety of participants, conducting detailed screenings for suicidal or homicidal ideation, plan, and intent where necessary. However, participants often present with other acute stressors such as food insecurity and housing instability that are beyond the scope of the role of research staff. In these instances, participants are provided with a detailed referral sheet and encouraged to seek out clinical staff at the CM program where appropriate.

ARTEMIS acknowledges that not all HIV-positive, methamphetamine-using MSM are ready, willing, or able to abstain from stimulant use. The focus of ARTEMIS on positive affect and non-substance-related sources of reward challenges the dominant paradigms of addiction treatment because it does not directly target psychological processes such as motivation that are traditionally conceptualized as being most relevant to reducing substance use. Instead, the positive affect intervention is designed to build the capacity of participants to cope more effectively with depression and other symptoms of stimulant withdrawal, which could maximize success with stimulant abstinence during CM and boost the long-term effectiveness of CM.

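### Per-visit comparisons of stimulant outcomes give up some precision because the CM urine results that every randomized man has before allocation are not used as a covariate

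*Protocol article*

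**What the plan says.** All places are in the Protocol article.

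- **Run-in period and randomization.** Before randomization each man completes a baseline assessment and "three urine screening visits (regardless of the toxicology results) at the community-based CM program". Men who do not finish the run-in are not randomized.
- **Discussion.** The HIPAA release allows the trial "to extract the CM urine screening results and CM incentives received from the clinical records".
- **Outcome analyses.** "Initial models will be unadjusted and compare outcome trajectories" between arms through the group-by-time interaction. Group differences at 3, 6, 12 and 15 months are also planned for primary and secondary outcomes: "These planned comparisons will be evaluated at α = .05". Covariate adjustment is mentioned only as a response to imbalance found in preliminary analyses, with propensity or marginal structural methods if that is not enough.
- **Recruitment, screening, and enrollment.** Entry requires that a man "provide a urine or hair sample that is reactive for methamphetamine metabolites".
- **Power analysis.** The statement covers viral load only, with a "total sample size of 150, 80 % retention, and four repeated measures of viral load".

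**The concern.** The run-in yields repeated biological measurements of stimulant use, taken before allocation and while the man is already in CM. By design they exist for every randomized participant. The CM program rewards samples free of methamphetamine and cocaine, and the urine outcome is a result reactive for either drug, so predictor and outcome measure nearly the same thing.

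The article states how covariates enter: by observed imbalance, not by expected prognostic value. Under that rule a strong predictor that happens to be balanced is never used, and its precision is lost. The choice of model also depends on the data. This is a stated rule, not a detail left to the SAP. At stake is power for urine toxicology and related stimulant outcomes, which the Discussion places on the pathway from ARTEMIS to viral load.

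**Working it through.** **1. The plan's own figure.** Inputs are 150 men, 80% retention (120 men, 60 per arm if allocation is 1:1), four measures and alpha 0.05. Two-sided testing and 80% power are assumed, since neither is stated.

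d = (1.960 + 0.842) × √[(2/60) × (1 + 3ρ)/4]

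- ρ = 0.1 gives 0.292.
- ρ = 0.8 gives 0.472.

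The stated 0.29–0.47 is reproduced. It concerns viral load and is not in dispute.

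**2. What a covariate buys at one visit.** If the run-in count explains a share R² of outcome variance, the residual SD shrinks by √(1 − R²). With 60 per arm the unadjusted detectable effect is 2.802 × √(2/60) = 0.511.

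| R² | Detectable effect | Power where unadjusted is 80% | 120 men act like |
|---|---|---|---|
| 0.05 | 0.499 | 82% | 126 |
| 0.10 | 0.485 | 84% | 133 |
| 0.20 | 0.457 | 88% | 150 |
| 0.30 | 0.428 | 92% | 171 |

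**3. Simulation of the month-3 urine.** Settings: 60 per arm, 50% reactive in control (assumed), 4,000 trials per cell, and a linear model with and without the 0–3 count. The latent correlation has a stable part plus a decaying part, both assumed. Power in %, unadjusted → adjusted:

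| Correlation (stable + decaying) | 50% v 35% | 50% v 30% | 50% v 25% |
|---|---|---|---|
| 0.2 + 0.2 | 39.0 → 40.3 | 61.6 → 63.6 | 81.3 → 84.2 |
| 0.3 + 0.3 | 39.4 → 44.1 | 60.8 → 65.7 | 82.4 → 87.1 |
| 0.5 + 0.2 | 39.5 → 48.4 | 61.2 → 72.3 | 82.0 → 90.1 |
| 0.6 + 0.2 | 38.6 → 51.2 | 61.5 → 76.1 | 81.4 → 93.1 |

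Gains run from 1.3 to 12.6 points, plus one cell at 14.6. Type I error with adjustment is 4.6–5.2%.

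Two further checks used different models:

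- A single-visit logistic model (60 per arm, latent correlation 0.25–0.64) went from 63.4 to 65.9, 67.1 to 71.2, 64.6 to 73.5 and 67.4 to 80.5%, gains of 2.5 to 13.1 points.
- A separate run (60 per arm, assumed latent correlations) gave about 2–11 points at month 3 and 1–7 at month 15. The gain fades as the run-in recedes.

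**4. The group-by-time interaction.** A covariate that is constant over time largely cancels from a contrast of change. Settings: 75 per arm, baseline plus four follow-up urines, 80% of follow-up observed, logistic GEE, latent correlation 0.3/0.4/0.5/0.6. Power was 90/91/91/94% unadjusted and 90/91/91/96% adjusted. For an arm-by-post contrast it was 38/38/38/45% against 38/39/37/45%. There is practically no gain.

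**The case against.** The strongest case against is that the unadjusted randomized comparison is valid, that covariates for secondary outcomes usually belong in the SAP, and that adding one is optimisation. The first part stands: nothing here biases the trial. The second stands only in part, because the article commits to unadjusted initial models and to imbalance as the trigger for adjustment.

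Four stronger readings are tempting, and the document does not support them.

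- **That power rises by 9 to 25 points.** Such gains arise in simulation for an arm effect averaged over four follow-up urines (71.3 to 80.2% at latent correlation 0.3; 56.0 to 81.0% at 0.6). The article names no such test. It names the group-by-time interaction, where the gain is close to nil, and per-visit comparisons, where it is moderate.
- **That entry selection leaves the screening sample with little prognostic value.** This would follow only if nearly all men entered on reactive urine. Men with non-reactive urine may enter by hair, in an unstated share. If 62–88% of admitted men were urine-reactive, the screening urine would have R² of 0.01–0.20 for a single follow-up visit. Under the same entry rules, including entry by urine alone, the run-in count has 0.02–0.32. A reactive CM urine can itself be the entry sample, so run-in urines may share the selection. Urine is also collected at each assessment, so a baseline-visit result may be available as well.
- **That chance imbalance in early abstinence goes uncorrected.** The plan compares potential confounders at baseline and foresees adjustment. The weakness is the trigger, not a total absence of adjustment.
- **That the primary analysis is underpowered or invalid.** The calculations concern stimulant outcomes only.

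**Conclusion.** The point holds as a modest, avoidable loss of precision in the per-visit comparisons of secondary stimulant outcomes. Adjusting for the run-in count would add roughly 1 to 13 points of power at a visit, with 15 in one favourable setting, and generally less at month 15 than at month 3. Almost no gain should be claimed for the group-by-time interaction.

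The direction was the same in every single-visit setting tried; the size is not derivable from the article. It rests on an assumed 50% reactive rate in control, assumed correlations between run-in and follow-up urines, 1:1 allocation, 60 men per arm with data, and reading the planned comparisons as differences in level at each visit. No calculation was made for self-reported use or craving; extending the covariate to them is reasonable but not quantified.

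**What to change.** - Pre-specify the number of reactive run-in CM urines (0–3) as a covariate in the comparisons of urine toxicology at 3, 6, 12 and 15 months, and by extension of self-reported stimulant use and craving.
- Add the baseline value of the outcome where it is collected.
- State that these covariates are chosen for prognosis and enter whatever the baseline balance.
- Define which three samples count. CM visits are thrice weekly and randomization is a separately scheduled visit, so some men may have more than three results by then; every sample counted must precede allocation.
- For binary outcomes report a standardized risk difference, so that the estimate remains population-level after adjustment.
- Show the unadjusted result alongside, and attach no claim of added power to the interaction test.

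The cost is a few lines in the analysis plan. The visits are already required and the release already covers extraction. The article describes a trial that is still enrolling, so the change can be fixed before outcomes are analysed.
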